### **7.1.3 Gametocyte quantification by qPCR**

These will be measured on Days 0, 3, 7, 14, 21, 28, 35 and 42. A small volume of whole blood (0.1 mL is preferred) from the finger stick will be placed in a cryovial and a suitable preservative will be added such as RNA protect or trizole. Gametocytaemia will be measured using a quantitative nucleic acid sequence based assay to detect male (Pfs230p) and female (Pfs25) gametocytes on a subset of patients. Samples will be analysed centrally at the KEMRI unit in Kilifi in Kenya and, possibly also, at MORU in Thailand.

### **7.1.4 Blood film for reticulocyte count**

A thin blood film will be stained with cresyl blue and read by an experienced microscopist. A SOP will be written for the preparations of these examinations in the field.

### **7.1.5 Full blood count, HemoCue & HCT measurements**

A full blood count will be measured on D0, 3, 7 and 28. Thereafter, Hb concentrations will be measured daily for inpatients and at every outpatient visit using the HemoCue system.

We will assess the accuracy of a simple to use, field adapted method for estimating the Hb concentration – the WHO (Copack) Haemoglobin Colour card. Blood will be taken at baseline, each follow up visit and when patients have recurrent parasitaemia. This will be done in Kinshasa only.

The HCT will be measured using a microcentrifuge.

### **7.1.6 Standard spectrophotometric quantification of G6PD enzyme activity**

This test requires a spectrophotometer and will be done using a suitable kit e.g. the G6PD enzyme assay from Trinity Biotech, USA or R & D diagnostics, Greece. This method reports the G6PD enzyme results as a change in absorbance over time. This value is normalised using the Hb concentration to give an enzymatic activity in U/g Hb. It will be done on D0. This method is considered the gold standard and will be used to assess the performance of the G6PD RDT and the G6PD Biosensor.

### **7.1.7 G6PD Biosensor**

We will assess the test characteristics of a G6PD quantitative biosensor. This point of care test can measure the G6PD activity using a drop of blood in few minutes. We will compare it to the standard spectrophotometric quantitative G6PD test on D0.

### **7.1.8 The G6PD rapid diagnostic test**

As described in Section 3.9, we plan to use the AccessBio G6PD RDT and assess its characteristics compared to the gold standard spectrophotometric method.

### 7.1.9 G6PD genotype

The A Glucose-6-Phosphate Dehydrogenase deficiency defined by G6PD 376 (rs) and G6PD 202 (rs) will be characterised from genomic DNA using the Agena MassArray IPLEX platform as previously described .

### 7.1.10 Characterising sickle cell disease and alpha thalassaemia

Genotyping for sickle cell disease and the common African form of alpha ( $\alpha$ ) thalassemia, caused by a 3.7-kilobase pair deletion in the  $\alpha$ -globin gene, will be conducted by PCR, consistent with published methods .

Children with one betaS ( $\beta^S$ ) mutation of the Hb gene will be classed as sickle cell trait (HbS) whereas homozygotes will be classed as sickle cell disease (HbSS). For  $\alpha$ -thalassemia, children with a single  $\alpha$ - ( $-\alpha / \alpha\alpha$ ) or two  $\alpha$ -globin deletions ( $-\alpha / -\alpha$ ) will be classed as homozygote and heterozygote for  $\alpha$ -thalassemia, respectively.

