### 2.2 Secondary Objectives

These are to:

- explore risk factors for developing profound or severe anaemia in this trial
- model the determinants of changes in haemoglobin concentrations over time
- characterise G6PD deficiency, other inherited blood disorders (IBDs) and the cytochrome 2D6 polymorphisms
- define the PK characteristics of PQ, cPQ, lumefantrine and piperaquine
- determine changes in gametocyte carriage over time
- measure the parasite clearance over time and the D42 cure rate

- assess the test characteristics of a G6PD Biosensor

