## 11 STATISTICS

### 11.1 Sample size

The sample size is based on demonstrating non-inferiority of ACT + SLDPQ compared to ACT alone with respect to the development of profound/severe anaemia in the G6PDd group. The rate of profound/severe anaemia in AL treated uncomplicated *P. falciparum* in Kinshasa is 1.5%.

For a non-inferiority margin of 2.5%, a two sided alpha=0.05 and a power of 80%, the sample size per group is 374 patients. Allowing for a 5% loss to follow up this become 393. We will recruit 800 G6PDd patients, the majority of whom will be males.

We will also recruit 800 patients into the G6PD normal arm, for a total sample size of 1600 patients. In the G6PD normal group, we expect the male-female ratio to be close to 1 and the age distribution to be very similar to that of the G6PDd group. The majority of malaria patients will be < 5 years old.

We plan to recruit a total of 1600 patients across both sites. Local ethical approval will be sought to recruit up to 1200 patients per site in case one of the sites experiences difficulties in recruitment.

Although genetic studies have shown relative high G6PDd allele frequencies, we are mindful of the weak correlation between G6PD genotypes and enzyme activities. Therefore, we have assumed a 10% proportion of G6PD RDT diagnosed G6PDd patients (most will be male) to calculate the number of patients we will need to screen ~8500 patients to obtain 800 G6PDd patients.

For other IBDs, we expect to recruit ~596 thalassaemia heterozygotes (prevalence 37.5%), ~246 sickle cell trait (15.7%), ~103 thalassaemia homozygotes (6.6%), and 14 sickle cell disease patients (0.9%).

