## 11.2 Analyses & analysis populations

All patients who received at least one dose of ACT and PQ/placebo will be included in the analysis. All analyses will be detailed later in a prospectively written analysis plan. Below is a summary.

The main strategy for analysis of the primary end point will be assessed by chi squared or Fisher's exact test, as appropriate, calculating the 95% CIs of the risk difference to see if ACT + SLDPQ has achieved non-inferiority in the G6PDd group. Logistic regression will be used to adjust for potential confounders. Non inferiority will be assessed on the whole data set i.e. combining data from both sites using the lower end of the 95% confidence interval. Other proportional data will also be analysed by chi squared or Fisher's exact test.

Continuous data (e.g. Hb, biochemistry, parasite counts) between two groups will be analysed by the unpaired 't' test, transforming the data, as needed.

All analyses will be two sided and a p value of < 0.05 is considered statistically significant.

We will examine factors that are associated with: (i) the development of profound / severe anaemia (logistic regression), (ii) parameters of Hb recovery (multiple regression). *A priori*, we will explore the relationships between Hb profiles in the following: (i) G6PD status (defined by genotype and by enzyme activity), (ii) any IBD vs. not, (iii) age <5 vs. age ≥5y, (iv) high biomass infections, assessed by microscopy and measured HRP2 concentrations, and (v) males vs. females. For these analyses, estimates and 95% confidence intervals (CIs) will be presented but not p values.

The PK data for PQ and cPQ will be analysed by non-compartmental analysis. The following PK parameters will be estimated:

- Cmax
- Tmax
- Clearance
- Half life
- AUC
- Vd

For lumefantrine and piperaquine, drug absorption kinetics will be modelled over the first 24 hours.

The Day 7 concentrations of lumefantrine and piperaquine will be compared between PQ and placebo recipients. Depending on the lumefantrine and piperaquine data obtained, other modelled PK parameters will be determined, as the data permit.

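### Protocol 7.1.10 reverses the two alpha-thalassaemia classes: one deletion is labelled homozygote and two deletions heterozygote

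*Protocol*

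**What the plan says.** Section 7.1.10 sets out how the genotyping results are to be classified. For α-thalassaemia it names two groups, children with one deletion (-α/αα) and children with two (-α/-α), and states that they "will be classed as homozygote and heterozygote for" the condition, respectively. The order is therefore explicit: one deletion is called homozygote and two deletions heterozygote.

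The sickle rule just before it runs the usual way. One β^S mutation is trait, "whereas homozygotes will be classed as sickle cell disease (HbSS").

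Section 11.1 gives the expected numbers in the trial: "596 thalassaemia heterozygotes (prevalence 37.5"%) and "103 thalassaemia homozygotes (6.6"%), against a plan "for a total sample size of 1600 patients".

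Genotypes of inherited blood disorders other than G6PD deficiency are a secondary endpoint in section 3.4. Section 2.2 includes an objective to "explore risk factors for developing profound or severe anaemia in this trial", and section 11.2 plans to study factors associated with "the development of profound / severe anaemia (logistic regression") and with haemoglobin recovery (multiple regression). It lists no covariates for either model. The only inherited-blood-disorder contrast that it names for haemoglobin profiles sets children with any such disorder against those with none.

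**The concern.** The sentence in section 7.1.10 is the protocol's only working rule for turning an α-thalassaemia genotype into a class, and it disagrees with the notation that it prints. A genotype of -α/αα has two different chromosomes, so it is heterozygous. A genotype of -α/-α has two identical ones, so it is homozygous. The rule says the opposite of both.

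The rule feeds a named secondary endpoint, so it is not background text. Anyone who builds the database or the genotype table from it would report the common class as homozygotes and the rare class as heterozygotes. In a model that keeps the classes apart, each coefficient would then be read against the wrong genotype. A reversed label leaves no missing value and no impossible code, so a routine data check would not catch it.

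**Working it through.** **Inputs.** From section 11.1: N = 1600; heterozygotes about 596 (37.5%); homozygotes about 103 (6.6%). From section 7.1.10: the classification rule and its order. My own assumptions: Hardy-Weinberg proportions for a single deletion allele in step 2, and a linear per-deletion effect in step 4. The protocol states neither.

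**1. Reproducing the protocol's counts.** Count = N × prevalence.
- 1600 × 0.375 = 600, against 596 stated.
- 1600 × 0.066 = 105.6, against 103 stated.

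Both agree within 3%.

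**2. Which labelling do the section 11.1 figures use?** Let q be the frequency of the deletion allele: q = P(two deletions) + P(one deletion)/2. The expected shares are 2q(1 − q) with one deletion and q² with two.

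| Reading of section 11.1 | q | Expected one deletion | Expected two deletions | Figures as read |
|---|---|---|---|---|
| Usual labels (one deletion 37.5%, two 6.6%) | 0.066 + 0.375/2 = 0.2535 | 2 × 0.2535 × 0.7465 = 37.8% | 0.2535² = 6.4% | 37.5% and 6.6% |
| Section 7.1.10 labels (one deletion 6.6%, two 37.5%) | 0.375 + 0.066/2 = 0.408 | 2 × 0.408 × 0.592 = 48.3% | 0.408² = 16.6% | 6.6% and 37.5% |

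The planning figures fit the usual labels almost exactly and are far from the section 7.1.10 labels. The error is therefore in section 7.1.10, not in section 11.1.

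**3. Children affected if the rule is applied literally.** 596 + 103 = 699, and 699/1600 = 43.7%. About 596 one-deletion children would be reported as homozygotes and about 103 two-deletion children as heterozygotes. The pooled total of 699 does not change.

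**4. Effect on a model that separates the classes.**
- *Genotype as an unordered factor, with no deletion as reference.* The two estimates keep their values and exchange their names.
- *Genotype as a score.* The correct score X is 0, 1, 2 deletions. The swapped score Z is 0, 2, 1. The frequencies are 55.9% (the remainder, 100 − 37.5 − 6.6), 37.5% and 6.6%. Suppose the true effect is b per deletion.
  - E(X) = 0.375 + 2 × 0.066 = 0.507
  - E(Z) = 2 × 0.375 + 0.066 = 0.816
  - E(XZ) = 2 × 0.375 + 2 × 0.066 = 0.882
  - Cov(X, Z) = 0.882 − 0.507 × 0.816 = 0.468
  - Var(Z) = 4 × 0.375 + 0.066 − 0.816² = 0.900
  - Least-squares slope on Z = b × 0.468/0.900 = 0.52b

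The slope keeps its sign and loses about half its size.

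**The case against.** The strongest reply is that this is a transposed word pair in an assay description, which trained staff would read past. The same sentence prints the genotypes, the sickle rule beside it runs the usual way, and section 11.1 has the classes in the expected proportions. The PCR assay observes the genotype itself, so a wrong label can be undone by recoding. Under section 12.4 thalassaemia is analysed only after the study is complete, so treatment during the trial does not depend on it. All of this stands. It makes the figure of about 700 children conditional on literal use of the rule, and it makes the harm recoverable. It does not make the rule correct, and recoding happens only if someone notices.

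Three stronger readings are tempting, and the protocol does not support them.

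- *A reader might infer that the planned risk-factor analysis will swap the two groups.* Section 11.2 lists no covariates for the logistic or multiple regression and plans no comparison of heterozygotes with homozygotes. Its one named contrast pools the classes. The swap follows only if a later model separates them.
- *A reader might infer that a trend across the number of deletions would be reversed.* The scores change from 0/1/2 to 0/2/1, and a linear trend is attenuated to about 0.52 of its size.
- *A reader might infer that everything except the pooled contrast is exposed.* The primary endpoint (section 3.3), the non-inferiority analysis in the G6PD-deficient group (section 11.2), the sample size (section 11.1) and the stratification by G6PD status (section 3.2) make no use of thalassaemia class.

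**Conclusion.** The rule in section 7.1.10 is wrong as written. Its own notation shows this without any outside source. The section 11.1 figures confirm the direction, given Hardy-Weinberg proportions.

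The consequence is limited to secondary results. Applied literally, the rule would misclass about 700 of 1600 children in the genotype endpoint and would mislabel the estimates in any model that separates one deletion from two. The figure of 0.52 for a trend rests on a linear effect, ordinary least squares, no other covariates and the protocol's own frequencies. It has not been worked out for a logistic model. The trial's safety conclusion on primaquine cannot change through this error, and nothing is lost that the raw genotypes could not restore. It is a minor to moderate point that is worth correcting because the error is certain and the correction is trivial.

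**What to change.** In section 7.1.10, exchange the two class names so that heterozygote comes first and homozygote second. The sentence then pairs -α/αα with heterozygote and -α/-α with homozygote, in agreement with section 11.1.

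In the data dictionary, store the genotype itself or the number of deletions (0, 1, 2), so that the class can always be derived and checked. This is a recording rule only. Whether genotype enters the haemoglobin and anaemia models as a factor, as a score or not at all can be left to the analysis plan.

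The cost is two words in the protocol and one line in the data dictionary. No sample size, primary analysis or patient management changes. If a genotype table has already been built from the present wording, its class labels should be checked against the raw genotypes.

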### 7.1.11 CYP 2D6 genotype

Several commercially available methods are available that use PCR platforms. We will select the specific platform at study end e.g. the Luminex system (Luminex® Corporation, USA). Allelic variation categories assayed by this kit include DNA sequences encoding normal metabolic function (\*1, \*2, and \*35), reduced metabolic function (\*9, \*10, \*17, \*29, and \*41), and non-functional (\*3, \*4, \*5 –for whole-gene deletion, \*6, \*7, \*8, \*11, and \*15), including DUP for duplication. The data will be analysed automatically using the xTAG Data Analysis Software TM to record the CYP2D6 allelic variant. A decision on which PCR system to use will be made nearer the time of analysis.

### 7.1.12 Percutaneous measurement of methaemoglobin

PQ causes a dose dependent rise in blood methaemoglobin (metHb). Daily PQ doses of 22.5-30 mg may produce metHb values of up to 18% which are well tolerated in healthy people . MetHb concentrations fall to normal concentrations within 7 to 14 days.

In Cambodia, 0.75 mg/kg of PQ base resulted in a modest increase of metHb – the maximum rise was 4.9% . The upper limit of normal is between 2-3%. Therefore, we do not expect that PQ in our study to result in clinically significant methaemoglobinemia.

A haemoximeter (e.g. Masimo Rad57 upgraded) will be used to measure the methaemoglobin content.

The following is a guide to the symptoms associated with methaemoglobinemia.

- Up to 2-3% Normal
- Less than 10% metHb - No symptoms
- 10-20% metHb - Skin discoloration only (most notably on mucus membranes)
- 20-30% metHb - Anxiety, headache, dyspnoea on exertion
- 30-50% metHb - Fatigue, confusion, dizziness, tachypnoea, palpitations
- 50-70% metHb - Coma, seizures, arrhythmias, acidosis
- Greater than 70% metHb - Death

### 7.1.13 Specimen labelling

Specimens and specimen tubes will be labelled as follows.

A label will be stuck onto the tube or specimen and the research team member will write:

- subject initials
- subject ID (study number)
- date and time of sample collection

- study day
- sample type e.g. plasma, serum etc.

For samples that will be sent out of the site, a bar code system will be used. One barcode label will be stuck to the sample tube / specimen and another bar code label to the sample log.

## 7.2 Primaquine, lumefantrine and piperaquine concentrations

There are no PQ/cPQ PK data in children <5 years so data from this trial will be crucial to determine whether the age based regimen in this study is suitable for children in this age group and allow us to compare PQ and cPQ exposures as a function of age and the ACT given.

The pharmacokinetics of PQ and cPQ will be characterised by non-compartmental analysis from blood samples at fixed time points. PK sampling will be done in Kinshasa and Uganda. The number of patients who will be sampled at each site will be 300:

- AL treated children aged < 5y (n=100)
- AL treated children aged 5-11 years (n=50)
- DHAPP treated children aged < 5y (n=100)
- DHAPP treated children aged 5-11 years (n=50)

Therefore, a total of 600 patients will be sampled. Approximately half will have received PQ and the other half placebo. Thus, the total number of patients with PQ PK data will be 300. We will keep a tally of patient numbers and once the required number of patients has been sampled we will stop the PK. Given the relative lack of children aged 5-11 years, we may not reach the sample size for this group.

For those children who received placebo, we will analyse the lumefantrine and piperaquine concentrations in the first 24 hours. We will insert an intravenous catheter at enrolment in children that will remain in place for 24 hours and draw up to a maximum of 8 samples per child (less if demanded by the local ethics committees) at fixed time points. Given the uncertainty of the outcome of the ethical review, we will select eight time points from this schedule: 0, 1, 1.5, 2, 3, 4, 6, 8, 10, 12, 24h.

Participation in this PQ PK sampling regimen is optional in Uganda but is considered part of the study in Kinshasa.

A venous blood sample for lumefantrine and piperaquine concentrations will be taken on D0, D3, D7, and D28

The sample size for lumefantrine is 200 – ~100 who will receive PQ and ~100 who will receive placebo. The sample size for piperaquine is also 200 with a 50-50 PQ-placebo split.

Comparing the D7 concentrations of both drugs between the PQ and placebo arms will determine whether PQ has affected their dispositions. Both lumefantrine and piperaquine D7 concentrations are valuable predictors of treatment failure in *P. falciparum*.

All PK samples will be analysed at the MORU PK laboratory in Thailand using MCMS / MS.

## 7.3 Sample Shipment

Any samples that cannot be analysed locally will be shipped to suitable laboratories for analysis in Thailand (e.g. MORU PK laboratory), Kenya (KEMRI-WT laboratories in Kilifi), the USA (PATH, Seattle), and the United Kingdom (e.g. Sanger Institute). All relevant shipping and local and international regulatory regulations will be followed.

## **8 SAFETY MONITORING & ADVERSE EVENTS**

Safety reporting will be done in accordance with MRC GCP guidelines. During the study, we will collect and record on the CRF symptoms, physical signs and laboratory findings. Data collection starts at study enrolment and finishes after the Day 42 follow up.

### **8.1 Adverse events & severity**

An adverse event (AE) is any undesirable event (symptom, sign, laboratory result) that occurs to a study participant during the course of the study; that is, from the time of study drug administration until study end. An AE may or may not be related to the study drugs, a concomitant drug or a study procedure.

An AE can be absent at baseline and newly develops or was present at baseline and worsens.

We will use the NIH Division of Microbiology and Infectious Diseases (DMID) toxicity table to grade adverse events from 1 to 4.

### **8.2 Relatedness of Adverse Event to study drugs**

Any AE that occurs will be assessed by the team physician to determine the relationship between the AE and the study drug/s. because two drugs are being used in this study, the AE may be related to one or both drugs.

This drug-AE relationship will be graded as follows:

- Unrelated: clearly not related to the study agent
- Unlikely related: doubtfully related to the study agent
- Possibly related: may be related to the study agent
- Probably related: likely related to the study agent
- Definitely related: clearly related to the study agent

### **8.3 Adverse Event Recording**

In this study, all adverse events of all severities will be recorded.

At each visit, study participants/their caregiver/legal guardian will be asked the open question “How is your child today?” Any reported symptoms will be recorded in the medical records.

On certain study days (see study schedule in Appendix 1), a symptom questionnaire will also be administered, entered into the database and analysed. If the research team physician thinks these symptoms require further evaluation, this will be done.

The investigator is responsible for the detection and documentation of events meeting the criteria and definition of an adverse event (AE) or serious adverse event (SAE).

All SAEs and AEs will be promptly documented from the moment of inclusion in the study to discontinuation of the patient from study participation. Any events occurring between screening and randomization will be considered as baseline, preexisting conditions.

All adverse events must be recorded in the AE/SAE CRF. To avoid colloquial expressions, the adverse event should be reported in standard medical terminology. Whenever possible, the adverse event should be evaluated and reported as a diagnosis rather than as individual signs or symptoms. If a definitive diagnosis is not possible, the individual symptoms and signs should be recorded. Whenever possible, the aetiology of the abnormal findings will be documented on the CRF. Any additional relevant laboratory results obtained by the Investigator during the course of this study will be recorded on the CRF.

If the event meets the criteria for “serious”, the SAE must be reported to the PAC safety team within 24 hours from the time that the event was identified. If further data is required, additional documentation can be submitted. All SAEs must be followed until resolution, or until the SAE is deemed permanent or leads to death.

